## Objectives

### Primary Objective

The primary goal of this study is to improve the intra-operative detection of peritoneal, omental and retroperitoneal metastases in ovarian cancer patients using ICG.

### Secondary Objective

The secondary goal is to determine whether additional peritoneal, omental, retroperitoneal ovarian cancer metastases can be detected with NIR fluorescent imaging after ICG injection.

## End points

**Primary End Point**

The primary endpoint is the percentage of peritoneal, omental or retroperitoneal ovarian cancer metastases identified with NIR fluorescence imaging (defined as the part of the pathology proven ovarian cancer metastases that also show NIR fluorescence)

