**Trial design**

Patients will be divided into two groups. One group with low stage ovarian cancer, and one group with high stage ovarian cancer. All patients in both groups will be administered ICG during at start of the surgery.

During surgery imaging with a NIR fluorescence camera system will be performed at different time points. After resection, NIR fluorescence imaging of the resected tissue will be performed at the pathology department.

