With modern imaging techniques, such as CT and MRI, preoperative localization and staging of tumors can be done reasonably well. However, preoperative imaging and gynecological examination alone are not sufficient in estimating whether a complete or optimal debulking can be carried out. Therefor in the Netherlands, it is currently investigated whether a preoperative laparoscopy can contribute to a better distinction between patients eligible for primary debulking and patients eligible for neo-adjuvant chemotherapy followed by interval debulking in advanced ovarian cancer.(3)

In patients with low stage ovarian cancer, detecting occult metastases has major implications for the treatment, as treatment of patients with metastasised disease involves chemotherapy after the surgical resection.(4)

In order to detect these metastases a staging surgery is performed. This involves taking biopsies of any adhesions surrounding the (area of the) primary tumour, all macroscopic suspect areas, blind biopsies of amongst others the peritoneum, and lymph node sampling. (www.oncoline.nl/epitheliaal-ovariumcarcinoom)

A recent development is the use of fluorescence imaging to visualize also tumors during surgery. This technique makes use of special fluorescent dyes, in combination with NIR light. This NIR light is not visible to the human eye, but can be detected with a camera system. The advantages of this technique are that it does not involve the use of harmful radiation, yet has a penetration depth of approximately 1 cm in tissue. One of the fluorescent dyes which is currently approved for clinical use is ICG. ICG is considered safe for use in humans and has been clinically used since the nineteen fifties for liver function tests and retinal angiography. Moreover, ICG has already been used in image-guided surgery research into detection of the sentinel node in breast, vulva and liver tumors with NIR fluorescence.(5)

Because in vivo ICG binds to serum proteins, it behaves as a macromolecule in the circulation. It is known that macromolecules accumulate in tumor tissue due to increased vascular permeability and reduced drainage in these tissues. This is known as the "enhanced permeability and retention" (EPR) effect.(6;7) In previous clinical trials in breast and gastric cancer patients it was possible to distinguish tumor tissue from the surrounding tissue using ICG in combination with optical imaging.(8-13)

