## Study design

All patients diagnosed with stage IIb t / m IIIc ovarian cancer eligible for debulking surgery will be included. In addition, all patients diagnosed with stage I or IIa ovarian cancer eligble for a surgical staging procedure will be enrolled.

All patients (n = 15) will be administered ICG (20 mg) during the surgery. Intraoperative NIR fluorescence imaging findings will be compared with clinical findings by the gynecologist during the surgery.

During the surgery, standard procedure will be followed and biopsies of clinically suspected areas will be obtained. Additional NIR fluorescent spots, that were not detected by the gynaecologist with usual visual/tactile methods, will also be removed and sent to the pathology department for histopathological assessment. Immediately after the resection, the resected tissue specimens will be transported to the pathology department of the LUMC, where specimens will be photographed and additional NIR fluorescent imaging will be performed. Hereafter the department of pathology’s standard procedure for assessing the resected specimens will be followed for both specimens detected under usual methods and specimens detected under NIR fluorescence imaging.

When it is decided by the attending gynaecologist to also perform a laparoscopic staging (whether or not in the context of the LAPOVCA study), a laparoscopic intra-operative NIR fluorescence imaging system can be used. (See umbrella protocol P10.001 protocol, version 3.0, Appendix 4 and 5 for a detailed description of the laparoscopic camera system).

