### Secondary End Points

- Tumor-to-background ratio between tumor and healthy tissue.
- Number of additional additional peritoneal, omental, retroperitoneal ovarian cancer metastases detected with NIR fluorescent imaging after ICG injection.

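### The primary endpoint counts a proven metastasis as identified if it fluoresces, without requiring contrast with adjacent tissue or that the signal be seen during surgery

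*Protocol*

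**What the plan says.** The End points section (Primary End Point), repeated in the Summary, makes the primary endpoint the percentage of metastases identified with NIR imaging, "defined as the part of the pathology proven ovarian cancer metastases that also show NIR fluorescence". The definition contains no minimum signal, comparator tissue or reader criterion, and it does not name the imaging occasion.

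Contrast appears elsewhere, as a separate secondary endpoint: "Tumor-to-background ratio between tumor and healthy tissue". It has no link to the primary count.

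There are several imaging occasions. The Summary (Trial design) states: "During surgery imaging with a NIR fluorescence camera system will be performed at different time points". The Study design section then sends tissue to the pathology department, "where specimens will be photographed and additional NIR fluorescent imaging will be performed".

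The Introduction gives the rationale. On the dye: "Because in vivo ICG binds to serum proteins, it behaves as a macromolecule in the circulation". On why tumour should show: "It is known that macromolecules accumulate in tumor tissue due to increased vascular permeability and reduced drainage in these tissues". On earlier studies in other cancers: "it was possible to distinguish tumor tissue from the surrounding tissue using ICG in combination with optical imaging". The Primary Objective is to improve detection of metastases during the operation.

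**The concern.** The endpoint's name and its definition measure different things. To identify a lesion during surgery, the surgeon must be able to pick it out from its surroundings on the image available at that moment. The definition asks only whether a lesion already proven by pathology also fluoresces.

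Two kinds of lesion can meet the definition without being detectable in that sense: one that fluoresces in vivo but no more than adjacent tissue, and one whose signal is seen only on the specimen after removal. Neither would have helped the surgeon find disease, yet both may add to the numerator.

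The primary percentage is the trial's lead measure of whether the technique works, from a pilot of 15 patients. If it includes such lesions, it overstates the intra-operative detection that the objective is about, and a reader could not tell by how much from the percentage alone.

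**Working it through.** The protocol gives no expected rate, threshold or formula for this endpoint, so there is no figure to reproduce. The check sets the text side by side and then follows the direction of the effect.

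**Step 1. Objective against rule.** The objective concerns detection during surgery. The Introduction's standard of success is distinguishing tumour from surrounding tissue. The endpoint rule contains neither element.

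**Step 2. Dye against rule.** The Introduction describes a protein-bound dye in the circulation that accumulates in tumour through permeability and reduced drainage. That mechanism gives relative retention, not exclusive uptake. The protocol does not state how bright normal tissue will be, but nothing in it rules out background signal, so the presence of fluorescence and contrast with neighbouring tissue are not the same criterion.

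**Step 3. Images against rule.** There are in vivo images at unspecified times and a further ex vivo image. The rule does not choose between them.

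**Step 4. Which lesions are affected.** The Study design section provides: "Additional NIR fluorescent spots, that were not detected by the gynaecologist with usual visual/tactile methods, will also be removed". Those lesions were necessarily seen as foci during surgery. The gap therefore concerns metastases removed on clinical grounds, whose NIR status is a separate classification made under the loose rule.

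**Step 5. Direction.** Among pathology-proven metastases, let

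- d = share seen in vivo as a focus brighter than adjacent tissue;
- f = share of the remainder that still shows some fluorescence, either in vivo without contrast or only ex vivo.

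Every lesion in d also shows fluorescence, so

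- written rule = d + (1 − d) × f;
- contrast-based, in vivo rule = d;
- excess = (1 − d) × f, which is never negative.

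**Step 6. Illustration on assumed values only.**

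| d | f | Written rule | Excess (points) |
|---|---|---|---|
| 50% | 0 | 50% | 0 |
| 50% | 0.5 | 50 + 50 × 0.5 = 75% | 25 |
| 50% | 1 | 50 + 50 × 1 = 100% | 50 |
| 20% | 0 | 20% | 0 |
| 20% | 0.5 | 20 + 80 × 0.5 = 60% | 40 |
| 20% | 1 | 20 + 80 × 1 = 100% | 80 |

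The documents give neither d nor f. The table shows that the excess can run from nothing to large; it does not predict where it will lie.

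**The case against.** The strongest reply is that contrast and intra-operative reading were plainly meant. The endpoint speaks of metastases identified with imaging. The Study design section refers to fluorescent spots, and a spot is something that stands out. The same section compares intra-operative NIR findings with the gynaecologist's findings. The Sample size section foresees that results might be negative in all patients, which would be odd if every metastasis were positive by construction. This probably describes the intent correctly. But none of these phrases is a criterion, and the definition that is given leaves both elements out.

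A second reply is that thresholds and reader rules belong in a statistical analysis plan or in the umbrella protocol to which the Study design section refers, neither of which is at hand. That holds for a numeric cut-off. It holds less well for the meaning of identified, which this protocol does not leave open but defines; adding a contrast requirement elsewhere would change a stated primary endpoint.

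A third reply is that the tumour-to-background ratio will be reported anyway, so poor contrast would be visible. This is a partial safeguard: it describes contrast but does not alter the count, and the text does not say that it is measured on every proven metastasis, including dark ones.

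Two stronger readings are tempting and should be resisted:

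- *The percentage will approach 100% because all perfused tissue fluoresces.* The protocol does not say so and gives no background signal, camera sensitivity or clearance. It is only the upper limit, f = 1.
- *The fluorescence call is made with histology known.* The Study design section and Figure 1 place NIR imaging before the histopathological assessment, and a pathology-proven denominator is the ordinary one for sensitivity. At most, the text does not exclude a later re-reading.

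**Conclusion.** The concern holds in a limited form. As worded, the primary endpoint lets metastases without usable contrast, or positive only ex vivo, count as identified, so it can overstate intra-operative detection. The direction is certain: the written rule equals or exceeds the share of metastases seen in vivo as a brighter focus. The size cannot be given from the documents, and it would be zero if the team applies the contrast that it probably intends.

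The conclusion rests on reading the bracketed definition as the operative rule, and on the inference from the dye's described behaviour that fluorescence and contrast can differ. It is a flaw in a stated definition, worth correcting because the primary percentage is otherwise hard to interpret. It does not show that the trial's result will be inflated.

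**What to change.** Amend the definition in the End points section and in the Summary so that a pathology-proven metastasis counts as identified only if it was recorded on the intra-operative NIR image, before the histology result was available, as a focus brighter than the adjacent tissue of the same site. Signal seen only on the specimen can be reported separately.

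Compute the planned tumour-to-background ratio for every pathology-proven metastasis, including those judged dark, with adjacent tissue of the same site as background, and report it beside the percentage. If the sponsor wants a numeric cut-off in the definition, it should be chosen in advance and justified; the documents contain nothing from which a particular value could be derived, and a pilot may reasonably do without one.

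The cost is a wording change, a per-lesion record of the call during surgery, and slightly more image analysis. The protocol does not say that in vivo images are kept, so retaining them for the ratio should be confirmed. The downside is a possibly lower headline percentage.

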# Introduction

Ovarian cancer is the 6th most common cancer among women. Worldwide every year 200,000 women are diagnosed with ovarian cancer. The prognosis of these patients is primarily dependent on the stage (FIGO staging) of the tumor, and of the accuracy of the surgical treatment. Patients with low stage ovarian cancer (FIGO I-IIa) have a 5-year survival of 75% -100%. The 5-year survival of patients with high stage ovarian cancer (FIGO IIb-IV) is 20% -60%. ([www.oncoline.nl/epitheliaal-ovariumcarcinoom](http://www.oncoline.nl/epitheliaal-ovariumcarcinoom))

Surgical resection and chemotherapy are the cornerstones of the treatment of ovarian cancer. For low stage ovarian cancer surgical resection of the uterus, adnexa and omentum is sufficient in most cases, provided that the surgical staging is optimally performed. In the Netherlands, no consensus exists on whether to give chemotherapy in case of low stage ovarian cancer with a grade III tumor. When staging is incomplete and restaging is not possible, low stage ovarian cancer is treated like high stage ovarian cancer with surgery followed by chemotherapy, due to the significant risk of micro metastases. (www.oncoline.nl/epitheliaal-ovariumcarcinoom)

However, about 70% of women present with advanced stage ovarian cancer (FIGO IIb-IV). The amount of tumor remaining after debulking is the most important prognostic factors in this group of patients and therefore the goal of surgery is to completely resect all tumor. After resection, these patients receive chemotherapy.(1)

In surgical debulking the aim is to leave no macroscopic residual tumor, and when this is not possible, to only leave residual tumor <1 cm in diameter. Complete surgical debulking is achieved when no tumor is visible after resection. After a complete debulking surgery, the survival rate is significantly better in comparison to optimal (<1 cm residual tumor), or sub-optimal (> 1 cm residual tumor) debulking surgery.(2)

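### The primary percentage includes metastases removed only because they fluoresced, while metastases missed by both sight/touch and NIR are under-represented, so it reads at or above the true sensitivity of NIR imaging

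*Protocol*

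**What the plan says.** The primary endpoint, worded identically in the Summary and in section 2.7, is a percentage of metastases identified by NIR imaging, "defined as the part of the pathology proven ovarian cancer metastases that also show NIR fluorescence". The denominator is every metastasis that pathology confirms, whatever led to its removal.

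Study design (section 2.4) gives two routes to pathology:

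- **Routine route:** "During the surgery, standard procedure will be followed and biopsies of clinically suspected areas will be obtained".
- **NIR route:** "Additional NIR fluorescent spots, that were not detected by the gynaecologist with usual visual/tactile methods, will also be removed and sent to the pathology department".

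The Introduction describes what standard surgery samples in low-stage disease. Staging includes "blind biopsies of amongst others the peritoneum, and lymph node sampling", and for treatment "surgical resection of the uterus, adnexa and omentum is sufficient in most cases". No comparable blind sampling is described for debulking patients.

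A secondary endpoint counts the additional "ovarian cancer metastases detected with NIR fluorescent imaging after ICG injection". Nothing takes those lesions out of the primary percentage.

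The Summary (Population) gives checking the technique's sensitivity as the reason for enrolling debulking patients. Section 2.3.3 plans 15 patients without a formal calculation and states no expected detection rate, lesion count or success threshold.

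**The concern.** A detection percentage can be read as sensitivity only if lesions enter the denominator regardless of the result of the test under study. Here one class of lesion enters because the test was positive. The opposite class, not fluorescent and not clinically apparent, enters only if blind or routine sampling happens to include it. This is selective verification. It is not incorporation bias, because the reference standard is histopathology and is applied in the same way to both kinds of specimen.

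What is at stake is the study's main product, the estimate. The distortion is strongest for occult metastases, which are the subject of the research question in the Summary, because there the NIR route supplies a larger share of the confirmed lesions.

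**Working it through.** The protocol states no detection figure, so there is none to reproduce. The direction can be derived from its text; the size needs assumptions.

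**1. Direction.** Among all metastases present, let F = fluoresces, C = found by sight or touch, B = in blindly or routinely sampled tissue. If every fluorescent metastasis is removed, the endpoint as written is

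E = P(F) / P(F or C or B).

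The denominator is at most 1, so E ≥ P(F), the true sensitivity, whatever the association between F and C. Equality requires every non-fluorescent metastasis to be verified.

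**2. Size under independence (all rates assumed).** With f = P(F), c = P(C) and b = the share of doubly missed metastases that blind sampling verifies,

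E = f / [f + c − fc + b(1 − f)(1 − c)].

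For f = 0.50:

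| c | b | E |
|---|---|---|
| 0.9 | 0 | 0.50/0.95 = 0.526 |
| 0.7 | 0 | 0.50/0.85 = 0.588 |
| 0.5 | 0 | 0.50/0.75 = 0.667 |
| 0.7 | 0.1 | 0.50/0.865 = 0.578 |
| 0.7 | 0.3 | 0.50/0.895 = 0.559 |
| 0.7 | 1 | 0.50/1.00 = 0.500 |

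Blind sampling reduces the excess, and removes it only when it is complete.

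**3. Dependence (assumed, c = 0.7, b = 0).**

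- P(F given C) = 0.7, P(F given not C) = 0.3: truth 0.49 + 0.09 = 0.58; E = 0.58/(0.70 + 0.09) = 0.734.
- P(F given C) = 0.3, P(F given not C) = 0.7: truth 0.21 + 0.21 = 0.42; E = 0.42/(0.70 + 0.21) = 0.462.

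The error is upward in both.

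**4. The same in counts (assumed).** Take 40 metastases found by standard methods, 20 of them fluorescent, so 20/40 = 50.0% among lesions found independently of NIR. Adding NIR-only metastases gives:

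- 5 added: 25/45 = 55.6%
- 10 added: 30/50 = 60.0%
- 20 added: 40/60 = 66.7%

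If blind sampling also finds 5 non-fluorescent metastases, the restricted figure is 20/45 = 44.4%, and the figures as written are 25/50 = 50.0%, 30/55 = 54.5% and 40/65 = 61.5%.

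**5. What restriction achieves.** In the two cases of step 3, restricting to clinically found lesions gives 0.70 against a truth of 0.58, and 0.30 against 0.42. The restricted figure is no longer selected by NIR, but it is not sensitivity among all metastases and can differ from it in either direction.

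**The case against.** **Doubly missed lesions do have a route in.** A reader might infer that they never enter the denominator. The documents do not support that: standard procedure is kept, and in staging patients blind biopsies, nodes and omentum give some NIR-independent tissue at all three endpoint sites. Resected specimens are also imaged again at pathology, so NIR-negative metastases in them can be scored. This stands, and is why the point is under-representation.

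**No occult-subset rate is planned.** A reader might also infer that the plan will report close to 100% among occult metastases. It defines one percentage over all confirmed metastases and a number, not a rate, of additional ones. A figure near 100% would also assume that blind sampling finds nothing. For example, take 5 fluorescent occult lesions out of 20. If 10% or 30% of the other 15 were verified, the rate would be 5/6.5 = 77% or 5/9.5 = 53%.

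**Restriction does not recover the truth.** Suppose 24 of 40 clinically found lesions and 5 of 20 occult ones fluoresce, with no blind sampling. The endpoint as written is 29/45 = 64%, the restricted one 24/40 = 60%, and the truth 29/60 = 48%. In the second case of step 3, restriction is further from the truth (0.30 against 0.42) than the current definition (0.462). This stands. The gain is a denominator that the test does not select, and the figure needs an honest label.

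**The data are largely collected, and an analysis plan could show both figures.** Study design already distinguishes specimens by how they were detected, and the secondary endpoint requires a count of the NIR-only ones. That makes the change cheap. It does not cure the definition, because the protocol itself fixes which percentage is primary.

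**The bias may be small beside the imprecision.** At clinical detection of 0.9 it is under 3 points for a true 50%. A naive Wilson 95% interval for 29/45 is about 50% to 77%, before allowing for clustering within patients. This bears on severity, not on direction.

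**Conclusion.** The point holds in this form: the primary percentage pools lesions that are NIR-positive by construction with lesions found by standard methods, and it under-represents those missed by both. It is therefore at or above the true sensitivity. The direction needs only that the fluorescent metastases are all removed and examined; it does not depend on how fluorescence and visibility are associated.

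The size is not derivable from the protocol. The range of about 53% to 67% for a true 50% rests on assumed clinical detection of 0.9 to 0.5, independence and no blind sampling; blind sampling narrows it.

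A reader might infer that the fault invalidates the study's conclusion. The documents do not support that: this is a 15-patient pilot with no success threshold, so an estimate is distorted and no formal decision is. It is a should-fix, not a must-fix.

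**What to change.** In section 2.7 and the Summary:

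1. Define the primary percentage over pathology-proven metastases in tissue taken for a reason independent of NIR: clinically suspect sites, standard resections, blind biopsies and nodes.
2. Label it as sensitivity among metastases found independently of NIR, and say that it may differ in either direction from sensitivity among all metastases.
3. Count metastases removed only because they fluoresced under the existing secondary endpoint for additional metastases.
4. Report the all-lesion percentage alongside as supportive, labelled an upper bound on sensitivity.
5. Record the reason for sampling and the in-situ NIR status of each specimen at surgery. Specimens are imaged both during the operation and at pathology, and the endpoint does not say which reading counts; it should.

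The cost is a wording amendment, one reason-for-sampling field per specimen, and possibly a less favourable headline figure. No extra tissue or patients are needed. The separation may not be recoverable later if the reason is not recorded at the time.

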**End points**

The primary endpoint is the percentage of peritoneal, omental or retroperitoneal ovarian cancer metastases identified with NIR fluorescence imaging (defined as the part of the pathology proven ovarian cancer metastases that also show NIR fluorescence)

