### Sample size

In this phase 2 pilot study, the value of NIR fluorescent imaging in detection of peritoneal, omental and retroperitoneal ovarian metastases after ICG injection will be studied. Because this study was designed as a pilot study no formal sample size calculation could be performed. Based on the heterogeneity of ovarian cancer metastases in the daily clinic, we expect a total of 15 patients will need to be enrolled. With this sample size we should be able to make a reasonable estimate of the feasibility of the detection of ovarian cancer metastases with NIR fluorescence imaging and ICG. If negative results are seen in all patients, we will consider stopping the pilot study prematurely.

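### The primary endpoint does not say which NIR look counts, nor require each lesion's fluorescence status to be recorded before histology is known, so it will tend to overstate intra-operative detection

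*Protocol*

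**What the plan says.** The Summary and the section on End points give the same primary endpoint. It is a percentage of metastases found by NIR imaging, and the bracketed explanation in both places reads "defined as the part of the pathology proven ovarian cancer metastases that also show NIR fluorescence". The Primary Objective is better detection during the operation.

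The document describes more than one look. The Summary (Trial design) states that "During surgery imaging with a NIR fluorescence camera system will be performed at different time points". Study design adds an ex vivo look at the pathology department, "where specimens will be photographed and additional NIR fluorescent imaging will be performed". Neither statement of the endpoint says which look decides whether a metastasis counts as fluorescent.

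Study design says three things about when NIR findings are read and used:
- "Intraoperative NIR fluorescence imaging findings will be compared with clinical findings by the gynecologist during the surgery".
- "Additional NIR fluorescent spots, that were not detected by the gynaecologist with usual visual/tactile methods, will also be removed"; these too go for histology.
- After the ex vivo imaging, the pathology department's "standard procedure for assessing the resected specimens will be followed for both specimens detected under usual methods and specimens detected under NIR fluorescence imaging".

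Figure 1 shows the same order: NIR imaging, resection, NIR imaging at pathology, then histology. Nowhere does the protocol require a fluorescence status to be written down for each removed lesion or specimen before its histology is reported.

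**The concern.** Acquiring an image before histology is not the same as fixing its reading before histology. The endpoint takes proven metastases as its denominator and asks which of them fluoresced. If that question is answered once the pathology report is in, the reader knows that every lesion being scored is a cancer. Doubtful signals are then more likely to be accepted than rejected.

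The choice of look raises a second problem. A metastasis that was not seen to fluoresce in theatre but does so on the excised specimen could be counted as identified, although the surgeon could not have used that signal. In both cases the reported percentage would no longer describe detection during surgery. That percentage is the main result of a 15-patient pilot that is meant to judge feasibility.

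**Working it through.** The protocol gives no expected detection rate, lesion count or threshold, and states that "Because this study was designed as a pilot study no formal sample size calculation could be performed". There is therefore no figure to reproduce. The check has two parts.

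**1. Which removed tissue has its NIR status fixed before histology?** Read from Study design and the description of staging surgery in the Introduction:

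| Tissue | Is NIR status fixed before histology? |
|---|---|
| Additional spots seen only on NIR | Yes. They are removed because they fluoresced, so every call is positive. |
| Clinically suspected lesions | Compared with NIR findings during surgery, but no recorded call is required. |
| Routine specimens, blind biopsies, sampled nodes | No call is required. |

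The only calls fixed by an action are positive ones. Every non-fluorescent metastasis must come from the second or third row. In the third row, a metastasis that neither the surgeon nor NIR imaging singled out first becomes known from the pathology report. If no status was recorded for that specimen in theatre, it can only be assigned afterwards, by someone who knows the answer.

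**2. In which direction would a late reading move the endpoint?** Let
- s = detection rate from calls fixed before histology,
- f = share of missed metastases changed to fluorescent on a later reading,
- g = share of positive calls withdrawn on a later reading.

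Then

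s' = s(1 − g) + f(1 − s),

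and s' exceeds s only if f(1 − s) > g·s. All values below are assumptions, because the protocol gives none.

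| s | f | g | s' |
|---|---|---|---|
| 0.50 | 0.10 | 0 | 0.50 + 0.05 = 0.55 |
| 0.50 | 0.25 | 0 | 0.50 + 0.125 = 0.625 |
| 0.70 | 0.10 | 0 | 0.70 + 0.03 = 0.73 |
| 0.70 | 0.25 | 0 | 0.70 + 0.075 = 0.775 |
| 0.70 | 0.25 | 0.10 | 0.63 + 0.075 = 0.705 |
| 0.70 | 0.10 | 0.10 | 0.63 + 0.03 = 0.66 |
| 0.90 | 0.10 | 0.10 | 0.81 + 0.01 = 0.82 |

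With upward changes only (g = 0), the endpoint rises. If positives can also be withdrawn, it can fall, as the last two rows show. A reader who knows that every lesion in the denominator is cancer has reason to upgrade misses and little reason to withdraw positives. That makes f large relative to g the likelier case, but it is a judgement about behaviour and not an algebraic result.

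The same formula covers the ex vivo look. If a positive on any look were accepted, g would be zero and every lesion fluorescent only ex vivo would add to the numerator. The protocol states no such rule, but it does not exclude one.

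With all calls fixed in theatre, f = g = 0 and the endpoint equals s.

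**The case against.** The strongest reply is that Study design already puts the reading in theatre. NIR findings are compared with the gynaecologist's findings during surgery, and a spot can be called additional only after it has been matched against the lesions found clinically. Ex vivo imaging also precedes the pathology work-up. This stands as far as it goes: it implies a theatre-time look at the clinically suspected lesions. It does not require a record of that look, it compares NIR with clinical findings and not with histology, and it does not reach routine or blind specimens that nobody suspected.

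A second reply is that reading rules may stand in a statistical analysis plan, a case report form or the umbrella protocol cited under Study design, none of which is at hand. For thresholds, readers and blinding that is fair, and no fault is claimed there. Which observation defines the primary endpoint belongs in the protocol, however, and an analysis plan cannot recover a call that was never recorded in theatre.

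Four stronger readings are tempting and are not supported:
- *That a late reading can only raise the percentage.* The calculation shows that it can fall.
- *That the protocol plans a retrospective reading.* No section provides for one; it is only not excluded.
- *That starting from proven metastases is itself the error.* That is how a sensitivity is defined. Benign lesions are in neither numerator nor denominator, so rereading them would not balance anything.
- *That a bias of a given number of points can be quoted.* Any such figure would rest wholly on assumed counts and rescoring rates.

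**Conclusion.** The concern holds in a limited form. The protocol leaves open which NIR look decides the primary endpoint. It also does not require the status of clinically suspected lesions and of routine or blind specimens to be recorded before histology is known. The numerator can therefore be settled with knowledge of the result, or from an ex vivo signal, and this will tend to overstate intra-operative detection. The direction rests on the assumption that a reader who knows a lesion is cancer upgrades misses more readily than withdrawing positives, or that ex vivo positives are counted. The size cannot be derived from the document; the tabulated values show only how the formula behaves.

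This is a small pilot with no hypothesis test or success threshold, so no formal decision turns on it. The safeguard is still worth adding because it is cheap and cannot be supplied after the operation.

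**What to change.** - **Summary (End points) and Primary End Point:** define a metastasis as identified only if it was recorded as fluorescent intra-operatively, before its histology result was known.
- **Study design:** require a yes/no intra-operative NIR call for every resected or biopsied lesion or specimen at removal, including clinically suspected lesions and routine or blind specimens. Deposits found only on sectioning take the call recorded for their specimen or site; without this rule they would have no call at all.
- **Reporting:** give ex vivo and any later readings separately. They do not change the recorded call.

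The cost is one more recorded item per specimen and a short addition in each of these places, with no extra patient or procedure. The percentage may come out less favourable. For a large specimen such as the omentum, a single call credits or discredits all deposits within it, so recording by site is preferable where feasible. Recording the call does not itself define what counts as fluorescent; that criterion may stand in the analysis plan or an imaging manual.
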